## Abstract

**Background:**

Chile has a high prevalence of postpartum depression and a significant treatment gap. Some barriers to postpartum depression care uncover the need for more easily accessible and lower-cost interventions. Chile's high utilization of digital technologies across all social strata and the increased use of pregnancy and parenting apps open the possibility of delivering interventions through mobile devices. Cognitive-behavioral internet-based interventions have proven to be effective in reducing symptoms of depression in high-income countries. However, in Chile, this is an underdeveloped field. This manuscript describes a randomized controlled trial protocol that will examine the feasibility and acceptability of a guided 8-week cognitive-behavioral app-based intervention for Chilean postpartum women with depressive symptoms.

**Method:**

A small-scale parallel 2-arms trial will be conducted. Postpartum women with minor or major depression will be randomized to the app-based intervention or waitlist. The primary outcomes are feasibility and acceptability variables, mainly; recruitment and eligibility rates, intervention and study adherence, and participants' intervention satisfaction, use, and engagement. Semi-structured interviews with a sub-sample will provide more information about the participants' experience with the intervention. Women's depression status will be assessed at pre-treatment, post-treatment, and 1-month follow-up. Other secondary outcomes will include participants' perceived social support, mother-infant bonding, and maternal satisfaction and self-efficacy.

**Discussion:**

This will be the first internet-based intervention aimed at reducing postpartum depression symptoms developed and studied in Chile. If the intervention and procedures prove feasible and acceptable, we plan to study its efficacy in a definitive controlled trial. If the intervention demonstrates to be effective, the aim is to implement it within the Chilean healthcare setting.

## Background

1

Maternal mental health problems pose significant global public health challenges (Hahn-Holbrook et al., 2018). Among these problems, postpartum depression (PPD) is the most common condition (Bydlowski, 2015). A meta-analysis of 291 studies using the Edinburgh Postnatal Depression Scale (EPDS) on 296.284 women from 56 countries found a global prevalence of PPD of 16.7 %, with significant heterogeneity across nations, ranging from 3 % (2–5 %) in Singapore to 38 % (35–41 %) in Chile (Hahn-Holbrook et al., 2018).

PPD is a devastating mental illness because it affects the whole family (Letourneau et al., 2012); it is associated with overall poor maternal health and impaired maternal functioning (O'Hara and McCabe, 2013; Gjerdingen and Yawn, 2007; Slomian et al., 2019). Impairments in maternal functioning are associated with difficulties in mother-to-infant bonding that may reduce the quality of the mother-infant relationship, which is critical for infant development and mental health (Stein et al., 2014; Slomian et al., 2019). Children of mothers with depression show a higher risk of developing insecure and disorganized attachments (Hayes et al., 2013) and a higher risk of developing depression throughout life (Pawlby et al., 2009). Evidence shows that the negative consequences in the quality of the mother-infant interaction are present even when the depressive symptomatology is subclinical (Tronick and Reck, 2009; Weinberg et al., 2001).

Psychotherapy is recommended as the first-line approach for both antenatal and postpartum depression (perinatal depression, hereafter: PND). It may be combined with pharmacotherapy, depending on depression severity, available options, and women's acceptance (Molenaar et al., 2018). In Chile, two studies have assessed interventions for PPD treatment (Olhaberry et al., 2015; Rojas et al., 2007). Rojas et al. (2007) group psychoeducational intervention showed significant improvement in low-income mothers with PPD compared with those in the usual care group. However, the attendance to the group sessions was meager; the mean number of group sessions attended was 2.7 out of 8, even though the research team offered a person to look after the participant's child during the sessions. The impression of the group coaches was that women liked attending groups, but too many pressing daily difficulties competed with their attendance (Rojas et al., 2007). Olhaberry et al. (2015) intervention consisted of a 4-session video-feedback intervention for mother-baby dyads on women with different levels of depressive symptomatology (from mild to severe). They found a significant increase in maternal sensitivity but no reduction in depressive symptoms.

In Chile, some advances in public policies have sought to improve mothers' and babies' wellbeing. In 2011, maternity leave was extended from 12 to 24 weeks. Additionally, since 2014, all women attending public healthcare facilities are screened for perinatal depression with the EPDS (twice during pregnancy and twice postpartum). However, despite the efforts to apply a protocol for universal PPD screening, early detection, and referral to mental healthcare services (Ministerio de Salud, 2014), there is still a significant treatment gap (Rojas et al., 2018). Barriers to addressing PPD have been identified on different levels (Dennis and Chung-Lee, 2006; Goodman, 2009; Byatt et al., 2012; Byatt et al., 2013; Rojas et al., 2015). At the patients' level, they include misunderstandings or negative beliefs about PPD and psychological treatments, stigma, and fear of being judged as an unfit parent, concerns about the risk of antidepressant use, lack of time or energy, lack of social support, childcare issues, lack of confidence on healthcare professionals and economic barriers. At the perinatal healthcare professionals' level, barriers include a lack of time for further psychological assessment and adequately communicating the diagnostic suspicion during check-ups, in addition to a lack of training in mental health.

In Chile, patients diagnosed with depression by a general practitioner have guaranteed access to treatment at low or no cost. Treatment varies according to depression severity, with group or individual therapy, alone or combined with pharmacotherapy. Nonetheless, public health providers' barriers to mental health care include long waiting lists, a frequency and duration of sessions below international recommendations, and a high rotation of professionals (Rojas et al., 2015; De la Parra et al., 2019). There is, therefore, an urgent need for user-friendly, easily accessible, low-cost, evidence-based psychological interventions to reduce the burden of PPD (Lee et al., 2016).

Nowadays, women are increasingly using the internet as a source of health information during pregnancy and postpartum, regardless of their socioeconomic status (Guerra-Reyes et al., 2016; Slomian et al., 2017). The widespread ownership of mobile phones globally has also prompted attention from the health field on the potential of delivering information and interventions through smartphones (Lal, 2019). Apps are particularly valued because of their convenience, immediacy, and ease of access (Lee et al., 2016). Women around the globe (including Chilean women) are engaging with pregnancy and parenting apps, which are almost becoming a routine part of the maternity experience (Hughson et al., 2018; Franco et al., 2023). This growing use of internet resources for health information is aligned with a trend in the world today: people are more in the lead of their healthcare, and this requires innovative ways of support (van Gemert-Pijnen et al., 2018). Thus, the internet and digital technologies have the potential to reach an enormous number of women who are already seeking information online.

Internet-based psychological interventions have the potential to overcome logistical and financial barriers both on the part of healthcare providers and patients, holding promise for cost-effective interventions (Krausz et al., 2019). Over the past decade, this field has grown in high-income countries (Lal, 2019) and shows a slow but progressive presence in other countries like Chile (Jiménez-Molina et al., 2019; Rojas et al., 2019). Advances in Chile have been facilitated by the fact that digital technologies are now highly utilized across all social strata (SUBTEL, 2021; SUBTEL, 2022). On the other hand, the growth of this field in the country is especially relevant for low-resource health services located in rural, hard-to-reach areas with no specialized mental health care nearby (Rojas et al., 2019).

Internet-based interventions have proven to be effective. Karyotaki et al.'s (2021) conducted an ‘individual participant data’ network meta-analysis that included 39 randomized controlled trials on internet-based interventions for depression (including PND). The meta-analysis demonstrated that both guided (including some form therapeutic support, either synchronous or asynchronous, delivered by a professional or a paraprofessional) and unguided (self-help or with automated support) interventions are associated with a greater reduction in depressive symptoms than treatment-as-usual and waitlist at post-treatment. Differences are maintained at six months and 12 months following randomization. Regarding internet-based interventions exclusively for PND, preliminary findings suggest that they may effectively reduce depressive symptomatology in perinatal women. Mu et al.'s (2021) meta-analysis showed that internet-based interventions could decrease the prevalence of perinatal depression and alleviate depressive symptoms in perinatal women (overall effect size of d = 0.64).

Although internet-based interventions for PND show promising results, they face adherence problems even when the intervention is guided (O'Mahen et al., 2013a; O'Mahen et al., 2013b; Lee et al., 2016; Lau et al., 2017; Forsell et al., 2017). One issue identified to work on is how to appropriately tailor the internet-based intervention's design to ensure usability, acceptability, and engagement among target users while retaining clinical effectiveness (Nicholas et al., 2017). Recent research on intervention development suggests integrating theory- and expert-based approaches with other methods that promote the involvement of the user (and other possible key stakeholders) from an early stage of intervention development and throughout the different stages of the process (van Gemert-Pijnen et al., 2011). The same has been suggested by studies that have assessed mothers' use and preferences for internet-based interventions or resources (Walker et al., 2017; Guerra-Reyes et al., 2016; Ramphos et al., 2019).

### Aims of the study

1.1

We developed *“Mamá, te entiendo” (“Mom, I get you”),* a guided 8-week cognitive-behavioral app-based intervention. The development of the intervention followed the “CeHRes Roadmap” (van Gemert-Pijnen et al., 2011), a multidisciplinary framework for guiding the development and assessment of eHealth derived from evidence-based strategies (including designing from user-based and persuasive approaches). This study aims to evaluate the feasibility and acceptability of “*Mamá, te entiendo*” through a small-scale randomized controlled trial. This intervention targets postpartum women with minor and major depression. Its aims are reducing depressive symptoms in the general sample and preventing major depression onset in women with minor depression. The feasibility outcomes will provide data to estimate the parameters required to design a definitive randomized controlled trial for assessing intervention efficacy (Arain et al., 2010). A qualitative process evaluation will be included to gain insight into participants' perspectives on the study procedures and intervention.

## Methods and design

2

### Study design

2.1

This is a mixed-methods feasibility and acceptability study of an app-based intervention for reducing postpartum depression symptoms. A two-arm, small-scale randomized controlled trial will be conducted with postpartum women with minor or major depression. Women will be randomly assigned to the intervention group (internet-based intervention: “*Mamá, te entiendo*”) or the control group (waitlist: WL). The three primary data collection points for study participants in the intervention group and WL group are as follows: baseline (pre-treatment: T0), post-treatment (8 weeks from randomization: T1), and 1-month follow-up (12 weeks from randomization: T2). See Fig. 1 for a detailed overview of assessment points. All assessments will be administered online through video calls (interviews) and web platforms (self-report questionnaires). A qualitative evaluation will be conducted to have more knowledge about participants' perspectives on the intervention and study procedures. The study has been registered in Clinicaltrials.gov (https://clinicaltrials.gov/) as NCT05643898 (December 2022) and received ethical approval from the Health Sciences Ethical Committee of Pontificia Universidad Católica (Santiago, Chile; protocol ID 210824004).

**Fig. 1 f0005:**
[figure not shown]
Study flow.

### Participants

2.2

Women will be included if they: have a baby between 1 and 7 months of age, have a PHQ-9 (Kroenke et al., 2001; Diez-Quevedo et al., 2001) score ≥ 5 points, have minor or major depression according to the Mini-International Neuropsychiatric Interview (MINI: Sheehan et al., 1998; Ferrando et al., 2000), are at least 18 years old, are Chilean residents, are fluent in written and spoken Spanish, self-reported ownership of a smartphone, and self-reported regular access to the internet. Minor depression will be defined as the presence of two to four concurrent symptoms of depressive disorder (one of which is depressed mood or anhedonia) present most or all the time for at least two weeks, with symptoms causing dysfunction and negative impact on the individual's life (American Psychiatric Association, 2013). Major depression will be defined as the presence of five or more concurrent symptoms of depressive disorder (one of which is depressed mood or anhedonia) present most or all the time for at least two weeks, with symptoms causing dysfunction and a negative impact on the individual's life (American Psychiatric Association, 2013). Participants' exclusion criteria will be the following: illiteracy, moderate or high risk of suicide, history of alcohol or substance abuse since they found out about the pregnancy to date, lifetime history of bipolar disorder or psychotic disorder, and current psychotic features.

### Sample size

2.3

As feasibility studies are not expected to test statistical significance, the usual power calculation for clinical trials is not normally undertaken (Arain et al., 2010). However, some authors suggest using a sample size of 25 per group for pilot studies (Whitehead et al., 2016). Based on these recommendations and anticipating a possible dropout of 30 %, a sample size of 33 participants per group was set.

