### Randomization

2.6

Women who meet inclusion criteria will be randomized to “*Mamá, te entiendo*” or WL. An independent person not involved in the study will generate the allocation sequence. Stratified randomization will be conducted according to depressive symptom severity (minor or major depression). To generate the random allocation sequence, we will use the software Study Randomizer (2017) using permuted block randomization with block size of 6 in a 1:1 ratio. Researchers will be blind to the randomization process and will be notified through email regarding participant allocation by an independent researcher. Once randomized, participants and research personnel will not be blinded to group condition, except for T1 and T2 interviewers. Following the notification, participants will be contacted by email to inform them of their assigned group (i.e., intervention or WL). The intervention group will receive instructions for registering into the app.

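### Sample size (2.3): 33 per group does not retain 25 per group at the stated 30% dropout; it leaves about 23 and retains 25 only if dropout is at most 24%

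*Protocol article*

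**What the plan says.** The whole justification of the sample size stands in section 2.3 of the protocol article. For a feasibility study, it says, "the usual power calculation for clinical trials is not normally undertaken". It then relies on a published rule of thumb: "some authors suggest using a sample size of 25 per group for pilot studies". Starting from that, and "anticipating a possible dropout of 30" per cent, it concludes that "a sample size of 33 participants per group was set", which is 66 women in all. It gives no inflation formula and no other reason for 33. Section 2.6 fixes equal allocation, "using permuted block randomization with block size of 6 in a 1:1 ratio", with stratification by minor or major depression. No other section explains or amends the figure.

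**The concern.** A dropout allowance is meant to ensure that, after the expected losses, the intended number of participants is still there. Here the stated loss applied to the stated size does not return the stated starting figure, so a reader who checks the sentence finds that it fails on its own numbers.

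Three things are at stake, all modest:

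- A reader will take the design to tolerate 30% dropout while keeping 25 per group. It tolerates about 24%.
- Attrition is itself among the primary feasibility outcomes (Table 1), so the observed rate is likely to be read against the planning figure in 2.3.
- The trial is meant to supply parameters for a definitive trial (section 1.1). If the same way of inflating were reused there, the shortfall would scale with the target: at 30% dropout, 1.30 × 0.70 = 0.91, so 9% of the target would be lost before rounding, whatever its size.

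**Working it through.** **Inputs, all from section 2.3**

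- Starting size: n = 25 per group.
- Anticipated dropout: d = 0.30.
- Stated size: 33 per group.

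No alpha, power, effect size or SD is given, and none is needed.

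**Step 1. Reproduce the stated figure.** Adding the dropout percentage to the target gives n × (1 + d) = 25 × 1.30 = 32.5, rounded up to 33. This matches. The formula is inferred, because the text does not state one.

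**Step 2. The size that retains 25.** If N women are randomised to a group and a fraction d is lost, N × (1 − d) remain. Setting N × (1 − d) = n gives N = n/(1 − d) = 25/0.70 = 35.7, rounded up to 36 per group, or 72 in total. Check: 36 × 0.70 = 25.2. The gap to the stated size is 3 per group and 6 in total, too large to be rounding.

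**Step 3. What 33 delivers at 30% dropout.** 33 × 0.70 = 23.1, so about 23 women per group, roughly 2 short of 25. This step does not depend on how 33 was obtained.

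**Step 4. The dropout that 33 tolerates.** 1 − 25/33 = 0.242. A group of 33 can lose 8 women (8/33 = 24.2%) and still have 25.

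**Step 5. Chance of keeping 25.** Assume that each woman drops out independently with probability 0.30. The binomial probability that a group keeps at least 25 is then about 0.30 with 33 randomised and about 0.61 with 36.

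**Step 6. Effect on precision.** For an interval computed only from women still responding in one group, the width changes by a factor of about √(25/23.1) = 1.04, or 4% wider. For the dropout rate itself, the denominator is everyone randomised. At a true rate of 30%, the simple 95% half-width per group is 1.96 × √(0.30 × 0.70/33) = 15.6 percentage points with 33, and 1.96 × √(0.30 × 0.70/36) = 15.0 points with 36.

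**The case against.** **The text never calls 25 a number of completers.** This is true. Section 2.3 cites 25 as a suggested size and attaches no such word to it, so the retained-number reading is inferred, as is the multiplication by 1.30. The inference is nevertheless firm: if 25 meant women randomised, no dropout allowance would be needed and 33 would have no basis.

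**Hardly anything depends on having 25 completers.** This largely stands.

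- Most outcomes in Table 1 are counted over women screened or randomised: eligibility, completion of assessments, dropout, modules completed, homework sent. The CEQ-6 is taken at baseline. For these, 33 per group already exceeds 25.
- The between-group comparison of depressive symptoms is by intention-to-treat with imputation of missing data in a random-effects model (section 2.11), not a completer analysis, so the 4% in step 6 does not describe it. Imputation does not recover lost observations, but the article ties no precision claim to 25.
- The qualitative sub-sample is purposive and has no fixed size (section 2.9.1.4).

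What remains exposed are measures taken only at T1, the CSQ-8 and TWEETS (Table 2), which need women who still respond.

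**The observed dropout rate does not depend on the inflation formula.** This also stands. The rate will be estimated from those randomised, and step 6 shows that its precision barely changes.

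**A tempting stronger reading** is that the trial is underpowered or fails to meet a declared design property. The article does not support this. It disclaims a power calculation, states no precision target, and sets no progression threshold that turns on 25 women per group.

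**Conclusion.** The figure is wrong as written, and the consequence is minor. On the article's own numbers, 33 per group leaves about 23 at 30% dropout, and 25 only if dropout is at most 24%; retaining 25 at 30% takes 36. The shortfall is about two retained women per group.

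The conclusion rests on one assumption, that 25 is the number to be retained. It does not rest on the inferred formula, because 33 less 30% is about 23 by any route. Nor does the error show that the 25 or the 30% is itself mistaken: both may stand, with 33 as the miscalculated figure. The point should be corrected because the slip is plain and the repair is nearly free. It gives no reason to doubt the planned analyses.

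**What to change.** Correct the sentence in section 2.3 and leave enrolment as it is. Suggested wording: *33 participants per group gives about 23 retained per group at 30% dropout, or 25 per group if dropout is at most 24%.* The cost is one sentence and a slightly less favourable stated figure.

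Only if the sponsor wishes to keep both 25 retained and a 30% allowance does the number change, to 36 per group (72 in total, six more women). Block size does not decide between the two: 66 and 72 are both multiples of 6. Because the blocks are stratified by minor or major depression, neither total guarantees that every block is filled.

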### Recruitment & screening for eligibility

2.4

Recruitment will be conducted online through advertisements on social media platforms. The ads will include general information on the study aims, inclusion criteria, and procedures, and will be linked to a web-based depression symptomatology assessment. Potential participants will be contacted for further eligibility assessment. No incentives for participation will be provided so that the endpoint of participant acceptability is not confounded.

#### Initial screening

2.4.1

The web-based initial screening will include brief information about the study, informed consent for this assessment, and the Patient Health Questionnaire -9 (PHQ-9: Kroenke et al., 2001; Diez-Quevedo et al., 2001) with automated feedback based on the obtained score. The automated feedback will function with the established score ranges of the scale: minimum, mild, moderate, and severe. Women will be encouraged to discuss their symptoms with their general practitioner or mental health specialist when there is a result of moderate or severe depression or a score of >1 point in question 9 (“Over the last 2 weeks, how often have you been bothered by thoughts that you would be better off dead or of hurting yourself in some way”; response options Not at all (0), Several days (1), More than half the days (2), and Nearly every day (3)). The feedback for women with suicidal ideation will include a dischargeable document with information on depression and mental health care resources. Women in the mild, moderate, and severe ranges will be informed that they are potentially eligible for the study and that they will be contacted for further assessment. Women in the minimum range or with >1 point in question 9, will be excluded.

In this initial screening, the PHQ-9 was used to assess depressive symptoms instead of the EPDS. This decision was made because we thought that women could be overly familiar with the EPDS. Moreover, as women are universally screened at 2 and 6 months postpartum, they could have answered the EPDS in a healthcare check-up recently.

